### Data monitoring and adverse events

A data monitoring committee is not needed due to the low risks associated with the interventions. The diet intervention group participants report symptoms or adverse events on their food diary, while the supervising exercise physiologist will document occurrence of the same during the exercise intervention. Intervention participants are also asked to contact study staff if any adverse events potentially related to the interventions occur beyond the intervention period. Serious adverse events will be reported to the study doctors and the ethics board. A statistician not associated with the study will perform an interim analysis of resting LVEF, as this is the standard parameter used to monitor cardiotoxicity within oncology practice. Resting LVEF will be compared between blinded groups after completion of the end of treatment assessment for the first thirty participants. These results will be unblinded, and along with documentation of adverse events, be provided to the study doctors who may make the decision to stop the study early if there is an increased risk or benefit deemed to be of clinical relevance at this time point. No auditing of trial conduct is planned. Participants who suffer harm from trial participation will be offered care by the study physicians.

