Intervention-related symptoms or adverse events	Food diary, Exercise session log	Will be collected for each intervention delivered				

*anth* anthracycline chemotherapy treatment, *CPET* cardiopulmonary exercise test, *ESAS* Edmonton Symptom Assessment System, *LVEF* left ventricular ejection fraction

^a^Typically measured before and after completion of all chemotherapy as standard of care

Secondary outcome measures include other parameters of cardiac function and structure (LV resting and peak strain, myocardial T1, LV volumes and mass, resting and peak cardiac output, peak LVEF, resting LVEF) and aortic distensibility at the end of anthracycline treatment, as well as circulating NT-proBNP at 24 h post the first and last treatment. Secondary skeletal muscle outcome measures include lower leg oxygen consumption and extraction, and thigh mass and quality at the end of anthracycline treatment. Secondary integrative outcome measures include whole body oxygen consumption reserve and treatment symptoms. Both interventions are hypothesized to reduce toxic effects on the heart, aorta, skeletal muscle and integrative measures relative to usual care.

A number of additional outcome measures of interest will be collected that are designated as exploratory. Exploratory outcomes at end of treatment include: 1) tumor size in neoadjuvant patients; 2) patient-reported quality of life and fatigue; 3) circulating markers of oxidative stress and antioxidants. To assess for potential longer-term effects of the interventions, a one-year follow-up with assessment of all MRI and questionnaire measures as well as CPETs and clinical outcomes (e.g. cancer recurrence, cardiac events, hospitalizations, mortality) will be completed. These combined clinical outcomes will also be collected as exploratory outcomes after five years of follow-up.

Safety outcomes will include clinically reported Edmonton Symptom Assessment scores throughout the intervention period as well as intervention-related symptoms or adverse events collected via food diaries and supervised exercise session monitoring.

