### Interventions

Caloric restriction intervention: Participants who are randomized to the caloric restriction arm will receive 48 h worth of prepared meals consisting of 50% of their daily caloric requirement. Caloric needs will be measured using resting energy expenditure (REE) assessed at baseline using indirect calorimetry in the morning after a 10–12 h water-only fast. Total daily energy expenditure will be calculated as REE multiplied by 1.4, which accounts for a low level of physical activity [56]. Participants will choose three isocaloric meals and two snacks consisting of half of the calories provided in the meals from a prepared menu with several options. Food will be freshly prepared within a day of the intervention for each participant at a metabolic kitchen, with each ingredient weighed to one-tenth of a gram. Each meal and snack will consist of North American macronutrient composition guidelines (30% protein, 20% fat, 50% carbohydrates) [57] calculated using Food Processor SQL (v11.0.3; ESHA Research, Salem, OR), and will be individually packaged and labelled. All food to be consumed within the 48 h period will be packed into an insulated cooler to be picked up by or delivered to the participant. To track adherence and adverse events, participants will be asked to keep a food diary to record any dietary deviations, as well as whether they experience any adverse nutrition impact symptoms (e.g., light-headedness, dizziness, nausea, diarrhoea).

Exercise intervention: Participants who are randomized to the exercise arm will perform a single bout of supervised aerobic exercise scheduled such that it would end approximately 24 h prior (window of 22–26 h allowed) to each of their scheduled anthracycline treatment times. The session will consist of a 10-min warm-up, 30 min performed at 70–75% of measured heart rate reserve, which corresponds to a vigorous intensity [51], followed by a 5-min cool-down. As an adjunct method of exercise prescription, the intensity will be adjusted as needed to maintain a minimum rating of perceived exertion (Borg 6–20 scale) of 13 (“somewhat hard”) and a maximum of 17 (“very hard”). An exercise physiologist will supervise the session one-on-one and will document any exercise-related symptoms or major adverse events.

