Usual care: As there are currently no clinical guidelines or recommendations on exercise timing or calorie reduction in relation to chemotherapy treatment, standard oncology care recommendations to maintain a pre-diagnosis exercise routine and diet throughout treatment was chosen as the comparator. Participants in this group will receive a phone call from study staff during each anthracycline treatment cycle to maintain engagement and enhance retention.

There may be potential for the two interventions to have a synergistic effect on our outcomes if they were combined. However, evaluating the independent impact, safety and efficacy of a caloric restriction versus an exercise intervention in humans is essential prior to combining these interventions. All participants will be asked to restrict any exercise performed on their own to light to moderate intensity for the 72 h prior and also for 48 h after each anthracycline treatment to isolate the effect of the pre-treatment exercise intervention. Compliance with this restriction will be assessed using a modified version of the Godin Leisure Time Exercise Questionnaire [58] for each treatment. Overall physical activity and dietary intake for the duration of the intervention period (~ 3 months) will be quantified and compared between groups by self-report using the Recent Physical Activity Questionnaire [59] and the Block Brief 2000 Food Frequency Questionnaire (Nutrition Quest, Berkley, CA). These questionnaires will also be administered at study entry and one-year follow-up with reference to their habits over the previous three months.

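### Non-serious adverse events are solicited only in the two intervention arms, by unlike methods and over unlike windows, yet the adverse-event records go into the interim stop decision

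*Protocol article*

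**What the plan says.** Two places in the protocol article set out how adverse events are collected.

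- **Outcome measures** names two kinds of safety outcome: symptom scores (ESAS) taken from clinical records, and "intervention-related symptoms or adverse events collected via food diaries and supervised exercise session monitoring". The timing entry in Table 2 for the second kind is "Will be collected for each intervention delivered".
- **Data monitoring and adverse events** gives the method by arm. For caloric restriction: "The diet intervention group participants report symptoms or adverse events on their food diary". For exercise: "the supervising exercise physiologist will document occurrence of the same during the exercise intervention". For anything later: "Intervention participants are also asked to contact study staff if any adverse events potentially related to the interventions occur beyond the intervention period".

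The Interventions section describes the one routine study contact with the control group between visits: "Participants in this group will receive a phone call from study staff during each anthracycline treatment cycle to maintain engagement and enhance retention".

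Data monitoring and adverse events also provides for an interim comparison of resting LVEF once the first thirty participants have had their end-of-treatment assessment. The unblinded result goes to the study doctors together with the documentation of adverse events. They may stop the study early if they see an increase in risk, or a benefit, that they judge clinically relevant.

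**The concern.** An adverse-event count reflects both how often events happen and how hard one looks for them. Here the looking differs by arm in four ways: who records (participant, staff, nobody stated), for how long, whether later reports are invited, and whether the event must first be thought related to the intervention. Because Table 2 ties the record to each intervention delivered, usual care cannot produce one.

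Among the symptoms the diary asks about are nausea and diarrhoea, which may have causes other than the diet. Without a control rate collected in the same way, the share due to the intervention cannot be separated from background.

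At stake is the interim decision. Risk can only be increased relative to something, and for these events nothing equivalent is recorded in the control arm. The article plans no data monitoring committee, so the study doctors weigh the material themselves.

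**Working it through.** The plan states no figure on this point, so there is none to reproduce. The check sets the collection rules side by side, sizes the difference in observation time, and asks which other sources fill the gap.

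**1. Collection rules by arm** (Interventions; Data monitoring and adverse events; Fig. 1 note for three cycles in most patients)

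| | Caloric restriction | Exercise | Usual care |
|---|---|---|---|
| Recorder | participant, food diary | exercise physiologist, session log | none stated |
| Active window per cycle | 48 h ("will receive 48 h worth of prepared meals") | 10 + 30 + 5 min = 45 min = 0.75 h | 0 h |
| Over three cycles | 3 × 48 = 144 h | 3 × 0.75 = 2.25 h | 0 h |
| Later events | self-initiated, only if potentially related | same | none stated |

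The ratio of active observation, diet to exercise, is 48 / 0.75 = 64. It is a ratio of hours, not of events or of bias.

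**2. When the windows close.** The diet covers the 48 h before treatment, and the session ends about 24 h before it (22–26 h allowed). Both close before the infusion, so nothing is actively asked about the days after it. The invitation to report later events is also unclear in reach: the Interventions section uses the term intervention period for roughly three months. On that reading, the days between sessions are covered by neither route.

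**3. Illustration of what unequal windows alone can do.** Assumption, not in the documents: the same constant symptom rate in every arm, with a proportion p of patients having a symptom in any 48 h. Then λ = −ln(1 − p)/48 and P(at least one record) = 1 − exp(−λt). With t = 144 h this is 1 − (1 − p)³. With t = 2.25 h it is 1 − (1 − p)^(2.25/48).

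| p per 48 h | Diet | Exercise | Usual care | Expected patients with a record, of 10 (diet / exercise) |
|---|---|---|---|---|
| 5% | 14.3% | 0.2% | 0% | 1.4 / 0.02 |
| 10% | 27.1% | 0.5% | 0% | 2.7 / 0.05 |
| 20% | 48.8% | 1.0% | 0% | 4.9 / 0.10 |
| 40% | 78.4% | 2.4% | 0% | 7.8 / 0.24 |

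The 10 per arm is 30 / 3 at 1:1:1 allocation. True rates are equal by construction, so the whole contrast comes from collection. Self-initiated later reports are left out. On these assumptions the distortion is mainly diet against the other two arms; exercise against usual care differs little.

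**4. Sources not limited by arm**

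- ESAS scores from clinical records over the intervention period: symptom scores, not adverse-event reports.
- Serious adverse events, and cardiac events, hospital admissions and deaths taken from records: serious outcomes only.
- Rotterdam Symptom Checklist: baseline, 2–3 weeks after the last anthracycline, and one year; not per cycle.

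These give a real comparison for serious harm and for symptom burden. They do not give a per-cycle record of non-serious adverse events gathered in the same way in each arm.

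**The case against.** The strongest defence is that the logs were never meant for comparison. They are labelled as intervention-related, they record how a meal plan or a session was tolerated, and usual care has neither. The only between-group comparison specified for the interim is resting LVEF. As a description of the logs this stands. It does not settle their use: the adverse-event documentation reaches the study doctors beside unblinded arm results, for a judgement about increased risk, and nothing restricts it to within-arm reading. The article's own aims also point to comparison. Interventions calls it essential to evaluate the safety of one intervention against the other, and Statistical analyses expects tolerance to help decide between them.

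Four smaller objections have weight:

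- Background symptoms may be low in the logged windows. Cycle 1 has no earlier anthracycline dose, and the Background section places the low point of symptoms on the day before treatment. The upper rows of the illustration may therefore be nearer the truth than the lower ones.
- Both intervention arms are asked to report later events, which softens the contrast in hours. That route is passive, filtered by presumed relation and closed to usual care.
- The article gives the purpose of the usual-care call, not its script. A fuller protocol could include adverse-event questions there. The rule as stated, however, ties collection to delivery of an intervention.
- A shared question set would not give perfect symmetry. The diet cooler may simply be picked up, the usual-care call has no fixed time in the cycle, and participants know their group.

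A reader might go further and infer that no safety comparison between arms is valid, or that harm after chemotherapy would have no comparator. The documents do not support either inference, because the sources in step 4 of the working cover all arms.

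**Conclusion.** The point holds for non-serious adverse events. As stated, they are solicited in two arms of three, by different methods and over 48 h against 45 min per cycle, with later reports left to the participant and filtered by presumed relation. Counts from the diaries, session logs and self-initiated reports cannot be compared between arms, and the plan does not keep them out of a stop decision taken on about 10 women per arm.

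The observation hours (144, 2.25 and 0 over three cycles) come from the documents for a patient with three cycles. The size of any resulting bias does not: the percentages in the working rest on assumed equal and constant rates and show only that a marked contrast can arise with no true difference. A reader might take 64:1 as the size of the bias; it is not.

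Serious events, extracted clinical outcomes, ESAS and the Rotterdam checklist remain comparable. This is a correctable weakness in the collection of safety data. It does not touch the primary outcome.

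**What to change.** Amend three places: the safety outcomes in Outcome measures (including Table 2), the Usual care paragraph of Interventions, and Data monitoring and adverse events.

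1. Ask one identical short adverse-event question set in all three arms once per cycle, at the same point in the cycle and by the same mode where possible, covering the time since the previous contact. Usual care can use the call already planned; the intervention arms need a matching brief contact, since collecting the diet cooler is not necessarily an interview. Ask again at the end-of-anthracycline visit.
2. Record every event regardless of presumed relation to the intervention.
3. Keep the food diary and session log as within-arm tolerability data, and say so.
4. State that between-arm safety judgements at the interim rest only on sources collected alike in all arms.

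The cost is a short checklist and a few minutes of existing staff time per participant per cycle, with no new visits. Participants still know their group, so some reporting difference may remain. If the question set cannot be added, item 4 alone would stop the unequal logs from being read as a comparison, but it would not supply the missing control record.

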### Randomization

Randomization will consist of a permutated block design with random block sizes of six and nine and stratification by two factors with a 1:1:1 allocation ratio. The stratification factors will include: 1) receipt of trastuzumab (yes/no), as it is also known to affect cardiac function; and 2) adjuvant/neoadjuvant protocol to ensure an equal distribution of neoadjuvant patients to assess the exploratory tumor size outcome. An external party to the study will generate the randomization sequence using a spreadsheet random function. This same individual will put the group assignment into sequentially numbered, sealed, opaque envelopes. Randomization will occur following completion of baseline assessments.

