### Outcome measures

The study outcome measures and their timing are summarized in Table 2. The primary outcome measure is cardiac function reserve capacity (LVEF reserve), which is calculated as peak exercise LVEF – resting LVEF, at the end of anthracycline treatment relative to the control group. Despite being the primary parameter used to diagnose cardiotoxicity, it is recognized that resting LVEF is insensitive to subclinical anthracycline-related cardiac damage due to the heart’s capacity to compensate for dysfunction at rest. By the time a decrease in resting LVEF is realized, there is likely already substantial and irreversible damage to the myocardium [3]. In women previously treated for breast cancer, a systematic review demonstrated that the application of either exercise or pharmacological stress during cardiac imaging techniques identified cases of cardiac dysfunction that were not identified using resting imaging [41]. More specifically, in women receiving anthracycline treatment for breast cancer, LVEF reserve (peak – rest) and peak LVEF after two treatments were significant predictors of a resting LVEF drop to < 50% at 18 months after treatment [42].

**Table 2 Tab2:** Summary of study outcome measures

Measure	Assessment Method	72+ h pre-anth	24 h post 1st & last anth	2–3 w post last anth	1 y post 1st anth	5 y post 1st anth
Primary Outcome:						
LVEF reserve (peak – rest)	MRI	x		x	x	
Secondary Cardiac Outcomes:						
Peak and resting LVEF	MRI	x		x	x	
Resting and peak LV strain	MRI	x		x	x	
LV volumes and cardiac output	MRI	x		x	x	
Myocardial T1	MRI	x		x	x	
LV mass	MRI	x		x	x	
NT-proBNP	Venipuncture	x	x	x		
Secondary Vascular Outcome:						
Ascending and descending aortic distensibility	MRI	x		x	x	
Secondary Skeletal Muscle Outcomes:						
Lower leg oxygen extraction	MRI	x		x	x	
Lower leg oxygen consumption	MRI	x		x	x	
Thigh muscle mass	MRI	x		x	x	
Thigh muscle quality	MRI	x		x	x	
Secondary Integrative Outcomes:						
Whole body oxygen consumption reserve	CPET	x		x	x	
Treatment symptoms	Rotterdam Symptom Checklist	x		x	x	
Exploratory Outcomes:						
Tumor size	Ultrasound	x		x^a^		
Quality of life	FACT-General questionnaire	x		x	x	
Fatigue	FACT-Fatigue questionnaire	x		x	x	
Markers of oxidative stress/antioxidants	Venipuncture	x		x		
Clinical Outcomes					x	x
Safety Outcomes:						
Clinically reported symptoms	ESAS	Will be extracted from clinical records for intervention period				

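### The interim lets the study doctors, shown unblinded arm-level resting LVEF on about 10 patients per arm, stop the trial for benefit at their judgement; it should be able to stop the trial only for increased risk

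*Protocol article*

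**What the plan says.** Under Data monitoring and adverse events, the protocol article decides against a data monitoring committee and plans one interim look: "A statistician not associated with the study will perform an interim analysis of resting LVEF". The reason given for the measure is that oncology practice uses it to monitor cardiotoxicity. The timing is also fixed: "Resting LVEF will be compared between blinded groups after completion of the end of treatment assessment for the first thirty participants".

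The same section settles who sees the result and what they may do. The results are unblinded and will, with the adverse-event records, "be provided to the study doctors who may make the decision to stop the study early if there is an increased risk or benefit". The criterion covers risk and benefit alike and rests on judgement: "if there is an increased risk or benefit deemed to be of clinical relevance at this time point".

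Under Outcome measures, the primary outcome is LVEF reserve (peak exercise minus resting LVEF) at the end of anthracycline treatment. It was preferred because "resting LVEF is insensitive to subclinical anthracycline-related cardiac damage". Sample size determination adds that reserve is expected to be the more sensitive of the two. Peak and resting LVEF are listed as secondary outcomes.

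**The concern.** The reason given for using resting LVEF at the interim is a safety reason. It justifies asking whether an intervention is harming the heart. It does not justify ending an efficacy trial early for success on an outcome that the article set aside as too insensitive to be primary.

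Two things are at stake. First, a benefit stop would be decided on about 10 patients per arm, where chance differences can be large, and it would leave the primary question with too few patients to answer it. An effect that triggers a stop at so small a sample also tends to overstate the truth. Second, if the trial goes on, doctors belonging to the trial know which arm looks better while others are still to be enrolled, treated or assessed in an open-label study. Peak LVEF, half of the primary outcome, is measured after exercise to volitional exhaustion.

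**Working it through.** **Inputs from the protocol article.** Interim after 30 participants; "stratification by two factors with a 1:1:1 allocation ratio" across three arms; 15 evaluable per arm, f = 0.25, three repeated measures and alpha 0.05; 56 enrolled. **Assumed, because the article does not give them:** the SD of resting LVEF (2.5 to 7 points) and the size of difference that would be called a benefit (3 points).

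**1. The plan's own power figure.** For the group-by-time interaction in a repeated-measures ANOVA, with correlation 0.5 between time points (assumed) and N = 45, λ = f² × N × m / (1 − ρ) = 0.0625 × 45 × 3 / 0.5 = 16.875 on 4 and 84 df. Power is 0.911, which agrees with the stated figure of over 90%. Enrolment is 45 / 0.8 = 56.25, against the stated 56. The sample size is not at issue here.

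**2. Size of the interim.** 30 / 3 = 10 per arm, which is 30/56 = 54% of those enrolled or 30/45 = 67% of those needed.

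**3. What SD is plausible?** The only precision statement, under Sample size determination, is that MRI can detect a 3-point change in resting LVEF with n = 15. If that means 15 per group, SD = 3 / [(z for alpha + z for power) × √(2/15)]. This gives 3 / (2.802 × 0.365) = 2.9 at 80% power and 3 / (3.242 × 0.365) = 2.5 at 90%. Both the per-group reading and the power are assumptions, so a wide range is shown.

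**4. Noise at the interim.** The standard error of an arm difference is SD × √(2/10). The 95% half-width is t(0.975, 27 df) = 2.052 times that, with the SD pooled over three arms. The null probability was simulated as the better of two intervention arms against one shared control.

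| SD (points) | SE | 95% half-width | P(at least one intervention ≥ 3 points better), no true effect |
|---|---|---|---|
| 2.5 | 1.12 | ±2.3 | 0.7% |
| 3 | 1.34 | ±2.8 | 2.4% |
| 4 | 1.79 | ±3.7 | 8% |
| 5 | 2.24 | ±4.6 | 15% |
| 6 | 2.68 | ±5.5 | 22% |
| 7 | 3.13 | ±6.4 | 27% |

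The trigger matters as much as the SD. At 2 points the probability is 7% at SD 2.5 and 35% at SD 6. At 5 points it is 0.5% at SD 4, 2.4% at SD 5 and 9.7% at SD 7.

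**5. Exaggeration.** Suppose the true benefit of an intervention is 1.5 points and the trial stops when that arm shows 3 or more. The mean observed difference among such stops is 3.7 points at SD 3 and 4.7 at SD 6, two to three times the truth.

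**6. What is left for the primary outcome.** Two-sample t test, two-sided 0.05, true difference 1 SD: power is 56% at 10 per arm and 75% at 15. The difference detectable with 80% power is 1.32 SD and 1.06 SD respectively. On the repeated-measures basis of step 1, but with 30 participants and only two time points, λ = 0.0625 × 30 × 2 / 0.5 = 7.5 and power is 0.64, against 0.91 as planned.

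**7. False claims if benefit meant nominal significance.** If benefit were read as two-sided p < 0.05 in favour of an intervention against control (the article does not say this), the chance of a false benefit would be about 4.5% at the interim and 4.5% at the end. For either one it would be 7-9%, depending on the correlation between resting LVEF and reserve.

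**8. Participants still to come.** 56 − 30 = 26, or 46%, at most.

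**The case against.** **Resting LVEF is a proper monitoring measure.** This stands. Using a familiar clinical parameter for safety and a more sensitive one for efficacy is no contradiction. Insensitivity to subclinical damage makes a real difference harder to see; it does not by itself create a false benefit. The chance of a false benefit comes from the small sample and the open criterion.

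**The noise may be small.** This stands in part. At the SD of about 2.5-2.9 obtained from one reading of the article's own precision statement, a 3-point chance benefit is rare, and the 3-point trigger is not in the article. A reader might infer that the interim is likely to end the trial on noise. The documents support only that it can.

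**Later data stay protected.** This stands in part. MRI reading is blinded to group and time point, staff doing the CPETs and biomarker analyses are blinded, and allocation uses sealed opaque envelopes. The article does not say what the study doctors do with later participants, so it does not support a reading that the interim does bias the rest of the trial. A route stays open, however. Participants and interventionists are unblinded, and the staff member who encourages the participant during the peak-exercise MRI is not stated to be blinded. Blinded reading cannot correct a difference in effort.

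**The missing boundary is a detail for the full protocol or analysis plan.** Agreed, and its absence is not counted here. The article itself fixes the measure, the recipients and the permission to stop for benefit.

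**The worst cases are worst cases.** This stands. Participants enrolled while the first 30 complete an intervention period of about three months would raise the 10 per arm and reduce the 26. The two-sample power figures are simpler than the planned mixed model, which is why the figure at 15 per arm is given beside them.

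**Conclusion.** The point holds in a limited form. The article permits a discretionary stop for benefit on a secondary outcome, at about 10 per arm, by study doctors who see the unblinded results. Nothing in the article supports the benefit half of that permission.

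How often chance alone would produce an apparent 3-point benefit depends on an SD that is not given: from about 1% at 2.5 points to 27% at 7. What a stop would cost the primary comparison is less uncertain: as few as about 10 per arm instead of 15.

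One further inference should be resisted. Because reserve is peak minus rest, a reader might conclude that a resting LVEF benefit necessarily lowers the primary outcome. That follows only if peak LVEF is unchanged, which the article does not say. Equally, the 7-9% false-benefit rate applies only if benefit means nominal significance. Bias in the remaining participants is a possibility to be closed off, not an established effect.

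**What to change.** 1. Delete the words *or benefit* from the stopping sentence, so that the interim can stop the trial only for increased risk.
2. State that the final analysis uses the full 0.05 because there is no efficacy look. A look that can stop only for harm spends none of the type I error for efficacy.
3. Have the independent statistician already named report the interim as a safety review. Arm-level LVEF should not go to staff who enrol, coach or assess later participants. The study doctors keep access to adverse events and to any safety signal. Withholding safety information from them altogether would be hard to defend without a monitoring committee, and it is not needed.

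The cost is a short amendment, made before the interim is run, using people already in the plan. What is lost is an early claim of success, which about 10 per arm on a secondary outcome could not credibly support.
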